#### Secondary outcome measures

We will evaluate the difference in secondary indicators between the treatment group and the placebo group from the following four aspects.
A pulmonary function test will be performed to evaluate the impact of PM2.5 on lung function in each subject (baseline, end of treatment, and 24 weeks).Early indicators of atherosclerosis, including IL-8 and ICAM-1, will be measured (baseline and end of treatment).The SF-36 questionnaire will be used to assess the health status of each subject and to generate a COOP/WONCA chart. The quality of life will be summarized for eight aspects: physical functioning, physical role functioning, physical pain, general health, vitality, social functioning, emotional health, and mental health (baseline, end of treatment, 12 weeks, and 24 weeks).Safety and adverse reactions to drug treatment will be monitored.

### Adverse events’ reporting and safety monitoring

The omega-3 fatty acids used in the project are a nutritional supplement with controllable safety risks. The Chinese Ethics Committee of Registering Clinical Trials (Ethical Review No.: ChiECRCT20190343) has approved this study. If the subject has any adverse events related to this study (such as diarrhea or nausea), it will be reported to the research team and recorded in the CRF. The project supervisor will also collect adverse events in a timely manner and decide on follow-up treatment (including close observation, additional medical management, or early termination).

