## Methods

### Study design

This is a randomized, single-center, placebo-controlled, double-blinded clinical trial. This research protocol complies with the standard protocol project: Interventional Trial Recommendations (SPIRIT) Guidelines (Additional Document 2). Eligible participants will be randomized 1:1 into two groups: the intervention group and the placebo group. Random numbers were generated by IBM SPSS Statistics V.25 software. The TH1/TH2 cell polarization index in the serum will be collected to determine the potential impact of people with high PM2.5 exposure. The Hospital of Chengdu University of Traditional Chinese Medicine (Sichuan Province, China) will serve as a research institution to the Chengdu Metro Company to recruit participants. The flowchart of this trial procedure is shown in Fig. 1. This study protocol has been approved by the Chinese Ethics Committee of Registering Clinical Trials (Ethical Review No.: ChiECRCT20190343). Before randomization, all eligible participants will be asked to sign an informed consent (see Additional file 3).

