Intervention group: Participants will receive treatment from the same batch of omega-3 fatty acids (1200 mg/capsule) provided by Kirkland, Canada. Participants will take two capsules every morning for 8 weeks and will be followed for 24 weeks after the trial. The omega-3 fatty acid capsules will be stored in a dry environment at room temperature.Placebo group: Participants will receive placebo treatment, containing soybean oil as the main ingredient, which has been produced by the Placebo Experimental Center of the School of Pharmacy, Chengdu University of Traditional Chinese Medicine. The physical appearance and weight of the placebo will be the same as the omega-3 fatty acid capsules, and the administration methods, experimental period, and storage methods will be identical to those in the intervention group.The capsules for the intervention group and the placebo group will be packaged in the same box. Each box will contain 8 weeks of drug dosage and will include the name of the subject, dosage, consumption schedule, description of storage conditions, and expiration date. “Experiment only” will be highlighted in a prominent position on the box. We have selected soybean oil as the placebo (comparison) agent because it is commonly used in daily cooking, its physical properties are similar to omega-3 fatty acids and it has no obvious effects on TH1/TH2 polarization [28].The drug to be used in this project is a nutritional supplement with controllable safety risks. The participant may do so if he/she has no adverse events or side effects. However, if the subject has diarrhea or nausea, their participation in the trial may be suspended and the adverse event will be reported to the research team. Due to the special nature of omega-3 fatty acids, we will prohibit participants from using antioxidant supplements, such as vitamin E, during the trial. Medications used by participants to treat other diseases will not be curtailed or changed. If omega-3 fatty acids are beneficial to subjects with high PM2.5 exposure, we will put the control subjects on the “waiting list,” that is, after the trial, the control subjects will also be provided with omega-3 fatty acids for 8 weeks free of charge.

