### Data and sample collection

We will use the Chinese Clinical Research Public Management Platform (Res Man) to collect and manage the data. The experimental data can only be accessed and manipulated by the research team.

The person in charge of the project will have access to the real-time data, but cannot make any changes to the data.

All data collectors will receive uniform training to ensure that data collected through questionnaires will have high quality and consistency. The Short-Form Health Survey 36 (SF-36) [29], designed to assess the quality of life through a comprehensive assessment of physical, mental, and social components and COOP/WONCA charts, will be completed at baseline, immediately after the final treatment, and then at 12 weeks and 24 weeks after the final treatment. A pulmonologist will collect data on pulmonary function from all subjects to ensure consistency prior to and following the final treatment, as well as 24 weeks after the final treatment. We also will examine the follow-up records for each patient regarding respiratory and cardiovascular diseases at 12 weeks and 24 weeks following treatment. The time frame for data collection and assessments is shown in Fig. 2.

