**Fig. 2 Fig2:**
[figure not shown]
Participant timeline

The number of TH1 and TH2 cells in the peripheral blood of subjects and the TH1/TH2 ratio will be measured at the time of enrollment (baseline) and again following treatment (8 weeks later). Similarly, we will determine the TH1/TH2 polarization state, including the concentrations of serum interferon-γ (IFN-γ), interleukin-4 (IL-4), interleukin-12 (IL-12), interleukin-6 (IL-6), interleukin-8 (IL-8), and intercellular adhesion molecule-1 (ICAM-1), as well as liver and renal function to assess drug safety, at baseline and following treatment.

The concentrations of TH1 and TH2 cells in the peripheral blood immune cell population will be detected by flow cytometry using a CytoFLEX Flow Cytometer (Beckman Coulter, Brea, CA, USA). Serum IFN-γ, IL-4, IL-12, IL-6, IL-8, and ICAM-1 levels will be measured using commercially available enzyme-linked immunosorbent assay (ELISA) kits. The nurse will collect the venous blood of the subjects, some will be stored in a 4 °C ice pack and immediately sent to the laboratory for testing (liver function and renal function), some will be stored at room temperature and sent to the laboratory for flow cytometry testing, and a part was frozen at −80 °C for ELISA detection. All blood samples will be assessed in the Laboratory of Hospital of Chengdu University of Traditional Chinese Medicine. The blood products of all subjects will be destroyed uniformly after the end of the study.

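### CRF recording is tied to study-related adverse events, while the next sentence collects adverse events without that limit, so unexpected harm can drop out of the between-arm safety comparison

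*Protocol article*

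**What the plan says.** All references are to the Methods of the protocol article.

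- **Adverse events' reporting and safety monitoring**, recording rule: "If the subject has any adverse events related to this study (such as diarrhea or nausea), it will be reported to the research team". The sentence ends with entry in the CRF.
- **Same section, next sentence**: "The project supervisor will also collect adverse events in a timely manner and decide on follow-up treatment". It has no relatedness condition. Its stated purpose is handling the case, and it does not mention the CRF.
- **Secondary outcome measures**: the list opens with "We will evaluate the difference in secondary indicators between the treatment group and the placebo group from the following four aspects", and its last item is "Safety and adverse reactions to drug treatment will be monitored". Safety is therefore one of the outcomes to be compared between arms, and part of it is named in causal terms.
- **Intervention**: "if the subject has diarrhea or nausea, their participation in the trial may be suspended and the adverse event will be reported to the research" […]. There is no relatedness condition, but only these two symptoms are named.
- **Data and sample collection**: laboratory measurements include "as well as liver and renal function to assess drug safety, at baseline and following treatment". For clinical disease, "We also will examine the follow-up records for each patient regarding respiratory and cardiovascular diseases at 12 weeks and 24 weeks following treatment".
- **Study design**: "This is a randomized, single-center, placebo-controlled, double-blinded clinical trial".

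**The concern.** In a blinded placebo-controlled trial, the comparison of event rates between arms is the main evidence on whether the product causes an event. If an event must count as related before it is recorded, part of that question is answered case by case, without knowledge of the arm, before the comparison is made. Events that are already expected pass easily, and diarrhea and nausea are the examples given. Unexpected events are the ones most likely to be left out.

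The CRF matters because Participant recruitment describes it as the place where trial data are recorded and then uploaded to the database. An event outside the CRF has no described route to the analysis. The exclusion criteria show that harms beyond the gut were considered: they cover a history of bleeding, allergy to fish or seafood, cholecystitis and gallstones. At stake is whether a safety outcome that the plan says it will compare between arms can detect harm of a kind not foreseen.

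**Working it through.** The point rests on wording. The article gives no adverse event rate and no power for safety, so there is no stated figure to reproduce.

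**Step 1. Which safety information depends on relatedness, and which reaches the CRF?**

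| Source (section) | Relatedness condition? | CRF entry stated? | Coverage |
|---|---|---|---|
| Recording rule (Adverse events' reporting) | Yes | Yes | Any event, if related |
| Supervisor's collection (same section) | No | No | Adverse events in general |
| Symptom report (Intervention) | No | Not in that sentence | Diarrhea or nausea |
| Laboratory tests (Data and sample collection) | No | As trial data | Liver and renal function, baseline and after treatment |
| Follow-up records (Data and sample collection) | No | As trial data | Respiratory and cardiovascular disease, 12 and 24 weeks after treatment |

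"As trial data" is not a quotation from these sections; it means that the general statement in Participant recruitment applies. The gap is what lies outside rows 3 to 5 and is presumed unrelated. A bleed, an allergic reaction or a gallbladder event in the 8 treatment weeks could fall there. Row 2 may catch such an event, but the text does not carry it into the CRF.

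**Step 2. Direction of the effect.** Let the true event rates be p_T and p_C, and let q be the share of events taken as related. Because the assessor does not know the arm, assume the same q in both arms. The recorded rates are then q·p_T and q·p_C.

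- Recorded risk difference = q·(p_T − p_C), which shrinks in proportion to q.
- Recorded risk ratio = p_T / p_C, which is unchanged.
- If p_T = p_C, the recorded difference is zero for every q, so no false difference arises.

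**Step 3. Illustrative size.** From the documents: 60 per arm (Sample size), and two-sided testing at 0.05 (Statistical methods). Assumed: p_T, p_C and q. Normal approximation:

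power = Φ[(d − 1.96·SE0) / SE1], where p1 = q·p_T, p2 = q·p_C, d = p1 − p2, p̄ = (p1 + p2)/2, SE0 = √[p̄(1 − p̄)·2/60] and SE1 = √[p1(1 − p1)/60 + p2(1 − p2)/60].

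Worked case, true rates 20% and 5%, q = 0.5:

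- p1 = 0.10, p2 = 0.025, d = 0.075, p̄ = 0.0625
- SE0 = √(0.0625 × 0.9375 × 2/60) = 0.0442
- SE1 = √(0.10 × 0.90/60 + 0.025 × 0.975/60) = 0.0437
- power = Φ[(0.075 − 0.0866)/0.0437] = Φ(−0.27) = 0.40

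| q | 20% vs 5%: difference (points) | Power | 30% vs 10%: difference (points) | Power |
|---|---|---|---|---|
| 1 | 15.0 | 70% | 20 | 79% |
| 0.75 | 11.3 | 56% | 15 | 64% |
| 0.5 | 7.5 | 40% | 10 | 45% |
| 0.25 | 3.8 | 22% | 5 | 24% |

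With the planned 20% dropout, 60 × 0.8 = 48 per arm remain. For 20% vs 5%, power is then 61% at q = 1 and 33% at q = 0.5.

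**The case against.** The strongest reply has four parts.

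1. *The text does not restrict collection.* The supervisor also collects adverse events, without a relatedness condition. This stands. A reader might infer that only related events are ever gathered, or that the rest are lost for good. The documents do not support that: a second route exists, and only its path into the CRF is unstated.
2. *Much safety information bypasses any filter.* This also stands. Liver and renal function, the respiratory and cardiovascular records, and diarrhea or nausea do not depend on attribution, and the outcome names safety in general beside adverse reactions. It would be wrong to say that the safety comparison as a whole is filtered. These sources do not cover other clinical events in the treatment weeks, however.
3. *No causality assessment is described.* True: no assessor or threshold is given, and the phrase on relatedness may have been meant loosely. That makes the rule ambiguous, which is itself a reason to reword it.
4. *This is a condensed article.* Event definitions and CRF fields may well be in the full protocol, and their absence here is no finding. The point is different: the article states a recording rule with an express limiting condition, beside a sentence without it.

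Two further inferences should be resisted. One is that the monitoring board would see only filtered events; Data management and monitoring does not say what it receives. The other is to take the 95% upper bound for zero events in 60, 1 − 0.05^(1/60) = 4.9%, and double it to 9.7% for 50% capture. That only restates the assumed capture rate.

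**Conclusion.** The concern holds in a limited form. As written, the CRF rule covers study-related events, the adjacent sentence collects events without that limit and without stating that they enter the CRF, and part of the compared safety outcome is framed as adverse reactions. Clinical events that are presumed unrelated and lie outside the laboratory, disease-record and diarrhea or nausea channels need not reach the between-arm comparison. Unexpected harm can be missed or diluted.

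The expected consequence is lost sensitivity, not bias toward either arm, provided the blind holds and attribution works alike in both arms. The size cannot be fixed from the documents because the share taken as related is unknown. For the assumed rates above, shares from 75% down to 25% reduce power from 70% to between 56% and 22%, or from 79% to between 64% and 24%. No figure in the plan changes.

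**What to change.** Reconcile the two sentences under Adverse events' reporting and safety monitoring. Suggested text:

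> All adverse events reported by participants or found at the planned contacts, in both arms, are recorded in the CRF whatever their presumed cause. Relatedness is recorded as a separate field, assessed without knowledge of the arm.

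State that events collected by the project supervisor enter the same CRF record. Align Secondary outcome measures so that all adverse events are compared by arm, with related events shown as a subset.

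The cost is slightly more recording at existing contacts. The change does not require more contacts, so completeness stays limited by the schedule: under Adherence to study interventions, weekly contact is made only where needed. It concerns data capture only and leaves clinical handling of events as it is.

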### Data management and monitoring

Data collection and monitoring will be managed by a dedicated Data and Security Monitoring Board (DSMB). The DSMB will be composed of a deputy chief physician from the respiratory department, a junior Chinese medicine practitioner, and a statistician, and these people are independent from the sponsor and competing interests. DSMB members will provide appropriate recommendations on the safety and completeness of all procedures during the clinical trial. They will occasionally monitor the progress of the research and ensure that the rights and well-being of the subjects are safeguarded. All completed questionnaires and laboratory results will be stored in a locked cabinet. The data will only be accessible to the researchers. Two data entry clerks will enter all data into an electronic database at the same time. The electronic database will be maintained as a password-protected file.

### Adherence to study interventions

Researchers will use varieties of strategies to encourage and monitor compliance with research interventions. During the 8-month research observation period, we will provide clear written instructions for the participants. The content will consist of adherence and lifestyle assessment guidelines to daily research capsule intake. If necessary, we will weekly contact all participants to evaluate how they manage the intervention and provide further personalized guidance. An independent drug administrator will take care of dispensing, recalling, storing, and recording all tested drugs.

### Statistical methods

IBM SPSS Statistics V.25 software will be used for statistical analysis of the data collected in this study. Subjects who withdrew from the experiment but received at least one treatment will still be included in the intention-to-treat analysis. We will use various attribution methods to conduct sensitivity analysis to test whether the results are reliable for different assumptions about missing data. Demographic and baseline data will be tabulated and evaluated using analysis of variance (ANOVA) or the *χ*^2^ test. Analysis of variance was performed on categorical variables, and the Pearson *χ*^2^ test was performed on continuous variables. Subgroup analyses will be performed according to the subjects’ working years (2–6 years, 6–10 years, and over 10 years) and average working hours per week (24–36 h and over 36 h). If conditions are appropriate, subgroup analysis will be performed with reference to the above criteria. 95% CI will be used for continuous variables. In this study, all statistical tests will be two-way, and a *P* value < 0.05 is considered valid.

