Located in southwestern China, Chengdu is a modern metropolis with a total population of more than 16 million. The Chengdu Metro, which has been in operation for more than 10 years, currently has 8 lines, with a total length of 358.235 km and 215 stations. In Chengdu, more than 1.4 billion commuters ride the subway each year (the Chengdu Metro Line Map is shown in Additional file 1). Previous studies have shown that short-term exposure to PM2.5 in subway systems may cause harm to humans [14]; however, few clinical studies have examined the effects of long-term exposure to PM2.5 among subway workers. To our knowledge, previous studies have mainly focused on physiological damage to humans caused by outdoor air pollution. Studies on subway employees exposed to PM2.5 are very rare. One study in China showed that the concentration of PM2.5 in the Chengdu subway was significantly higher than PM2.5 concentrations detected on city streets [15]. As the number of employees in the Chengdu subway system continues to increase, research is needed to assess potential harms that may result from PM2.5 exposure.

Omega-3 polyunsaturated fatty acids (PUFA), including eicosapentaenoic acid (EPA), docosapentaenoic acid (DPA), and docosahexaenoic acid (DHA), have been shown to produce a variety of beneficial effects on human health [16]. A large number of epidemiological studies and clinical trials have shown that consumption of omega-3 fatty acids may have beneficial effects by reducing inflammation and regulating the function of macrophages, neutrophils, T cells, and B cells [17, 18]. Studies have found that omega-3 fatty acids may regulate immune function and have beneficial health effects in clinical trials examining PM2.5 in indoor air pollution [19–21].

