### Sample size

G*Power 3.1 will be used to calculate the sample size necessary to have sufficient statistical power [26]. The sample size calculation will be based on a previous study of omega-3 fatty acids and their effects on up-regulating the TH1/TH2 ratio by ~ 32.5% [27]. The type I error is 0.05 and the power is 80%. Considering a dropout rate of 20%, we aim to recruit 120 subjects. The treatment group and the placebo group were assigned 60 participants each. Based on the grouping of our experiment, we will be divided into the high exposure group and low exposure group according to PM2.5 exposure. In the high and low exposure groups, 30 subjects were treated with omega-3 fatty acids and placebo.

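### Working years and weekly hours are banded for the subgroup analyses, although both are continuous; the bands lose some information, how much depends on unstated distributions, and the year bands overlap

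*Protocol article*

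**What the plan says.** Statistical methods in the protocol article fixes three bands for the first factor and two for the second: "working years (2–6 years, 6–10 years, and over 10 years) and average working hours per week (24–36 h and over 36 h"). It gives no reason for the cut points and names no analysis that keeps either factor continuous. The next sentence makes the analysis conditional: "If conditions are appropriate, subgroup analysis will be performed with reference to the above criteria".

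Other parts of the article bear on the bands:

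- The inclusion criteria for both exposure groups require at least 2 years in post, at least 3 working days a week and at least 8 h a day. The floors are therefore 2 years and 3 × 8 = 24 h a week.
- The Background describes "The Chengdu Metro, which has been in operation for more than 10 years", and Trial status puts the start of recruitment at November 1, 2020.
- Intervention and the inclusion criteria make half the sample (60 of 120) office staff working in filtered air. Randomization is stratified by exposure.

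**The concern.** Years in post and hours per week are the trial's two measures of time at work. The natural question for these subgroups is whether the omega-3 effect grows or shrinks along them. Bands treat a worker at 24 h as identical to one at 36 h, and one at 36 h as different from one at 37 h. If the effect changes gradually, the variation inside each band is thrown away and the answer depends on where the cuts fall.

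The bands also have faults of their own. A participant with exactly 6 years fits both of the first two. The top year band may hold very few people, because a metro described only as more than 10 years old may have few staff with longer service.

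What is at stake is the power and clarity of a secondary analysis.

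**Working it through.** **Is there a figure to reproduce?** No. The documents give no figure for information lost and no mean, SD or shape for either factor. Every distribution below is an assumption. Only the cut points (36 h; 6 and 10 years) and the floors (24 h; 2 years) come from the article.

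**Formula.** If the treatment effect is linear in the factor, the share of information kept by banding is the between-band variance of the factor divided by its total variance. The loss is 1 minus that share. For a normal factor cut once at the point c below which a share p lies, the share kept is φ(c)² / [p(1 − p)]. At p = 0.5 this is 2/π = 0.637, a loss of 36%; at p = 0.2 it is 0.490, a loss of 51%.

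**Weekly hours, cut at 36 h**

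| Assumed distribution | Share at or below 36 h | Loss |
|---|---|---|
| Only 32 h or 40 h (four or five 8-h shifts) | any | 0% |
| 24, 32, 40, 48 h in equal shares | 50% | 20% |
| Uniform 24–48 h | 50% | 25% |
| Uniform 24–56 h | 38% | 30% |
| Uniform 24–60 h | 33% | 33% |
| Normal, mean 36, SD 6, truncated at 24 | 49% | 35% |
| Normal, cut at its median | 50% | 36% |
| Normal, mean 40, SD 5, truncated at 24 | 21% | 50% |
| Normal, mean 40, SD 4, truncated at 24 | 16% | 56% |
| Normal, mean 44, SD 6, truncated at 24 | 9% | 68% |

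The second row by hand: the mean is 36 and the total variance is (144 + 16 + 16 + 144)/4 = 80. The band means are 28 and 44, so the between-band variance is 8² = 64. Then 64/80 = 0.80 is kept and 20% is lost. In the first row each band holds one value, so nothing is lost.

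**Working years, cuts at 6 and 10**

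| Assumed distribution | Shares in the three bands | Loss |
|---|---|---|
| Uniform 2–14 years | 33 / 33 / 33% | 11% |
| Uniform 2–12 years | 40 / 40 / 20% | 14% |
| 2 + exponential, mean 3 | 74 / 19 / 7% | 20% |
| 2 + exponential, mean 4 | 63 / 23 / 14% | 20% |
| Normal, equal thirds | 33 / 33 / 33% | 21% |
| Uniform 2–10.5 years | 47 / 47 / 6% | 21% |
| Normal, mean 6, SD 2.5, truncated to 2–10.5 | 49 / 49 / 2% | 28% |
| 2 + exponential, mean 2 | 87 / 12 / 2% | 29% |
| 2 + exponential, mean 2, truncated at 10.5 | 88 / 12 / 0.4% | 37% |

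**What this does to power.** As a yardstick, take a linear interaction that would have 80% power with the factor continuous, at two-sided 0.05 and 120 × (1 − 0.20) = 96 people. The plan does not claim this power for the subgroups. The noncentrality needed is about 8.0; multiplying it by the share kept gives:

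- Two bands split at the median: 61% power (normal) or 68% (uniform).
- Three equal bands tested on 2 df: 60% (normal) or 65% (uniform).
- Three equal bands tested as a 1-df trend: 70% (normal) or 75% (uniform).

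**Cell sizes.** Two arms by three year bands make six cells. On average 96/6 = 16 people fall in each, and 48/6 = 8 within the high-exposure group alone. The top band may hold fewer.

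**The case against.** The strongest reply is that little more than preference is at issue. The cut points are fixed in advance, so they cannot be chosen from the data, and the lower limits match eligibility. Bands do not impose the linearity that a slope assumes. The analysis is secondary and conditional. Modelling detail is commonly left to the full protocol or analysis plan, which is not shown. This is fair and keeps the point minor. It does not remove it, because the bands are stated in the article and an interaction test added elsewhere would not restore what banding discards.

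A reader might infer that a third or more of the information is lost on both factors. The documents do not support that. It is essentially the result for a normal factor cut once at its median. It overstates the three-band loss for years under most spreads, and it is no floor for hours, where the loss could be 20% or even nil.

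A reader might also infer that the plan announces a formal effect-modification analysis with a separate P value in each band. The article says only that subgroup analyses will be performed. That exact years and hours are recorded is likewise an inference from the eligibility criteria, though a strong one. The figure of 96 is a yardstick too, since withdrawn participants who received at least one treatment stay in the intention-to-treat analysis.

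One objection changes the remedy. Half the sample works in filtered-air offices, so their years and hours do not measure station-hall exposure. A single slope over everyone, without the exposure stratum, would mix the two kinds of time.

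**Conclusion.** The point holds as a minor improvement. The article bands two continuous factors, gives no reason for the cuts and names no continuous analysis. The two factors need separate statements of loss: for hours, from about 0–20% through 25–36% to 50–68%; for years, typically 11–29% and up to about 37% with a nearly empty band. All of these rest on a linear trend in the treatment effect and on assumed distributions.

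The overlap at exactly 6 years is certain from the text. The near-empty top band is only possible, because the stated age of the metro has no upper limit and the number of long-serving staff is not given. The primary comparison of omega-3 with placebo is not affected.

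**What to change.** For each factor, fit one model with treatment, exposure stratum (high or low), the factor as a continuous variable, and the treatment-by-factor interaction. Report the interaction slope with its 95% CI, and show it also within the high-exposure stratum, where time at work means time in the station hall. Keep bands for description only, and redefine them so that exactly 6 years belongs to one band.

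The cost is analysis-plan wording and no new data, provided exact years and hours are entered in the case report form, as eligibility checking implies. The downside is that approximate linearity is assumed; adding one curved term (for example a squared term) checks it. The slope within the high-exposure stratum rests on half the sample and will be imprecise, so it should be read as exploratory.
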